### Data safety monitoring committee (DSMC)

The DSMC will evaluate AEs on a semi-annual basis. The TITE-CRM model will ensure that the risk of grade 3–5 toxicity doesn’t exceed 35%. However, the DSMC will monitor the risk of related grade 5 toxicity occurring at any time within 1 year of treatment and will track all grade 5 toxicities reported within the 5 year follow-up period. If any dose level sustains 3 related grade 5 toxicities within the first 10 patients on that level, that dose level (and higher) will be closed.

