#### Dose assignment procedure

Accrual will start at Level 1 (recovery factor = 10% at 6 months + 0.75% per month thereafter). This recovery factor equation was selected as it translates to approximately 10%/year, which is used in common practice in many Canadian centres, and a lower starting dose may compromise local control for patients enrolled initially. The maximum dose level (Level 6, with 100% recovery at 5 years) was chosen as several studies have reported full-dose thoracic reirradiation. Further dose escalation beyond Level 6 may be investigated in future studies when more is known about recovery time dynamics and organ-specific tissue responses.

Patients will be assigned to recovery factors using the TITE-CRM model (Table 4). The model will use all available information from previously accrued patients to assign the highest dose with a predicted risk of grade 3 toxicity of 35% or less (a similar allowable toxicity level to phase I trials using 3 + 3 designs), with the additional restrictions outlined below.

In the TITE-CRM design, to allow the trial to remain open to accrual without interruption, and in order to use the maximum information from patients already accrued when assigning dose levels, data from patients who have not completed the 1-year follow-up period are weighted according to the proportion of follow-up completed. Weights will range from 0 to 1, with zero denoting no follow-up and 1 denoting 12 months of follow-up (e.g. a patient with 6 months of follow-up will be weighted as 0.5). Any patient with a grade 3–5 toxicity will be weighted as 1, regardless of length of follow-up.

The following restrictions on dose escalation will also be employed:Dose levels may only increase one level between consecutive patients;A patient may not be assigned to a higher dose level unless there is at least 2 years of cumulative observations on patients at the current dose level. This cumulative observation may be divided among several patients (e.g. four patients treated on Level 1 and followed for 6 months each would constitute 24 months of cumulative observation).

In situations where the required recovery allowed by the trial (e.g. 25%) is more than required by the oncologist to deliver the prescribed treatment, those patients will not be enrolled**.**

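### The DSMC section promises a 35% toxicity ceiling that assignment on a point prediction cannot deliver, and no action is stated when no level qualifies

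*Protocol article*

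**What the plan says.** Under *Data safety monitoring committee (DSMC)* the protocol article states: "The TITE-CRM model will ensure that the risk of grade 3–5 toxicity" does not exceed 35%. The next sentence then limits the committee's specific numeric task to grade 5 events.

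Under *Dose assignment procedure*, the model is to "assign the highest dose with a predicted risk of grade 3 toxicity of 35% or less" (the Abstract gives the same rule for grade 3–5). The section adds: "The following restrictions on dose escalation will also be employed". There are two:

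- "Dose levels may only increase one level between consecutive patients"
- no move to a higher level unless "there is at least 2 years of cumulative observations on patients at the current dose level"

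Both act on upward moves only. Nothing says what follows if all eight predictions exceed 35%.

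The one numeric closure rule is in the DSMC section: "If any dose level sustains 3 related grade 5 toxicities within the first 10 patients on that level", that level and those above it close. On timing: "The DSMC will evaluate AEs on a semi-annual basis". The committee also monitors related grade 5 risk within one year and tracks such events to five years, without a further threshold.

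**The concern.** A continual reassessment method steers towards a target rate. It does not bound the true rate at the level it assigns or finally selects. Here the promise stands where one would expect a boundary for grade 3–4 toxicity, so a DSMC reading the plan could believe that this risk is already controlled.

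The assignment rule can also have no solution. Accrual starts at Level 1, the third lowest of eight, so only two lower levels are available. If both are also predicted above 35%, the rule names no level and the plan is silent. That is the situation in which a phase I safety rule matters most, in patients having thoracic reirradiation and with an endpoint that includes death.

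**Working it through.** **The plan's own figures.** 8 levels × 6 = 48 patients. 48/16 to 48/12 = 3 to 4 years, the stated 36–48 months. Both reproduce. No operating characteristic is given for the 35% promise, so it was tested by simulation.

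**Inputs from the article.** Initial risks for Levels −1 to 6 from Table 4: 0.034, 0.048, 0.067, 0.094, 0.130, 0.181, 0.252, 0.350. Start at Level 1, linear weights over 12 months, toxicity weighted 1, both escalation restrictions, N = 48, and 14 patients a year (the middle of 12–16).

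**Assumptions not in the article.** Power model p_i(b) = s_i^exp(b), where s_i is the Table 4 risk. Normal prior on b with SD 1.16 (variance 1.34), or 0.75 as a sensitivity check. Posterior mean of b plugged in. Toxicity times uniform over the year. Lowest level used when none qualifies. 1,000 trials per scenario.

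**When the rule has no solution.** Level −1 is predicted above 35% when 0.034^exp(b) > 0.35, so exp(b) < ln 0.35 / ln 0.034 = 1.0498/3.3814 = 0.310, or b < −1.17. All higher levels are then above 35% too.

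**A tolerable level exists.**

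| True risks | Selected level above 35% | Patients treated above 35% |
|---|---|---|
| Level 2 is the MTD (.10/.15/.22/.32/.42/.50/.58/.65) | 43% (42% with SD 0.75) | about 17 of 48 |
| Level 4 is the MTD (.34, next level .44) | 29% | about 6 of 48 |
| Level 1 already at 40%, lower levels tolerable | 47% | about 23 of 48 |

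**Every level too toxic.**

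| True risks | No level qualifies at some point | No level qualifies at the final analysis |
|---|---|---|
| 40–68% | 92% (77% with SD 0.75) | 69% (62%) |
| 50–78% | 99% | 98% |

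A shorter rerun of the Level 2 and all-toxic curves (300 trials each) agreed to within a few percentage points.

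**Grade 5 closure rule.** P(at least 3 of 10) = 1 − Σ(k = 0 to 2) C(10,k) p^k (1−p)^(10−k). At p = 0.20 this is 1 − (0.107 + 0.268 + 0.302) = 0.32. At p = 0.10, 0.15, 0.25 and 0.30 it is 0.07, 0.18, 0.47 and 0.62. With 20–40% of toxicities assumed fatal, adding this rule still leaves a level above 35% selected in 45–37% of trials in the Level 2 scenario.

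**The case against.** **Some one-level overshoot is inherent in a 48-patient phase I trial, and the curves above are fairly steep at the MTD.** This stands. With a flatter curve (33% at the MTD, 38% at the next level), over-selection falls to 14–16% and 2–3 patients are treated above 35%. If Table 4 were exactly true, nobody would be, because its maximum is 0.350. This limits the size of the problem but does not make the promise true.

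**A reader might infer that the plan would treat all 48 patients when every level is too toxic, and then name an over-toxic MTD.** The documents do not support that. With no qualifying level, the text authorises no assignment, and the MTD definition requires a rate of 35% or less. Continuing at the lowest level was a simulation assumption. The fault is that the text is undefined.

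**A reader might infer that one early toxicity exhausts the levels.** That depends on the prior. One event in the first patient puts Level −1 at 40% with variance 1.34 but at 20% with variance 0.5. Two events in eight patients give 17% to 45% at variance 1.34, depending on the follow-up of the other six.

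**A reader might infer that grade 5 oversight ends after ten patients, or waits for six-monthly meetings.** Only the numeric trigger is confined to the first ten. Monitoring and DSMC discretion continue. Related grade 3–5 events are reported to the principal investigator and coordinating centre within one business day, and each related death enters the model with weight 1. The closure rule is not tied to the meeting dates.

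**The full protocol or a DSMC charter may hold operating characteristics and a stopping rule.** It may, and their absence from an article is not the complaint. The complaint is that the article states a guarantee which its own assignment rule cannot give.

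**Conclusion.** The point holds in this form. The assurance is wrong as worded, because the rule acts on a predicted risk with no bound on its uncertainty. The assignment rule as stated has no defined outcome when no level is predicted at or below 35%.

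Where a tolerable level exists, selection of a level truly above 35% runs at roughly 30–45% under the main assumed curves, and lower if the risk curve is flat near the MTD. Where all levels are too toxic, the rule usually reaches a point with no admissible level. The closure rule does not fill the gap: it does not address grade 3–4 toxicity, and at a true 20% death rate it misses a level in 68% of cases over its first ten patients.

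The simulated percentages rest on a model, prior and true risks that the article does not give. They show the order of the problem and are not this trial's exact operating characteristics. The falsity of the guarantee and the missing action do not depend on them.

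**What to change.** 1. In the DSMC section, say that the model *targets* a grade 3–5 risk of 35%. Give the simulated probability of selecting a level above 35% and the expected number of patients treated at such levels, under stated scenarios and the trial's actual prior.
2. In the dose assignment section, state that when no level qualifies there is no escalation and the DSMC is notified. The sponsor and DSMC should specify how assignment is then handled.
3. Suspend accrual for DSMC review when the posterior probability that the lowest level's risk exceeds 35% passes a cut-off calibrated by simulation, after a minimum number of patients.
4. Ask the DSMC to consider whether its grade 5 boundary should extend beyond the first ten patients per level. The threshold is the committee's decision.

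Pausing at every empty set would be a poor substitute for item 3. At variance 1.34 it would interrupt about 26–28% of trials in which Level 2 is a tolerable MTD, against the design's purpose of continuous accrual.

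An illustrative version of item 3, applied from patient 6 with prior SD 1.16:

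| True risks | Suspended, cut-off 0.90 | Mean N, cut-off 0.90 | Suspended, cut-off 0.95 |
|---|---|---|---|
| All levels 50–78% | 86% | 27 | 74% |
| All levels 40–68% | 42% | 39 | 27% |
| Level 2 is the MTD | 0.2% | 48 | 0% |
| Level 1 at 40%, lower levels tolerable | 5.5% | 46 | 1.9% |

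The cost is a few days of simulation and a protocol paragraph, a small tabulated chance of a false suspension, and only partial detection when all levels are modestly above 35%. The stopping criterion does not reduce over-selection when a tolerable level exists (44% in the Level 2 scenario), so the wording in item 1 has to change as well.

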### Statistics and sample size

#### Primary endpoint

The primary endpoint of this study is the MTD of radiotherapy for thoracic reirradiation implemented by sequentially increasing the normal tissue recovery factors applied to previously delivered dose. The MTD is the recovery factor equation associated with a ≤ 35% rate of grade 3-5 treatment-related toxicity occurring within 1 year of treatment. Refer to Table 3 for examples of treatment related toxicities.

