#### Recovery factor levels

Recovery factor levels are described in Tables 1 and 4.

**Table 4 Tab4:** Recovery factor levels

Level	Recovery After 6 Months	Rate/Month	Recovery After 1 Year	Recovery After 3 Years	Recovery After 5 Years	Estimated risk of DLT for initial TITE-CRM model*
−1	3%	+ 0.50%/m	6%	18%	30%	0.034
0	10%	+ 0.50%/m	13%	25%	37%	0.048
1	10%	+ 0.75%/m	15%	33%	51%	0.067
2	15%	+ 0.75%/m	20%	38%	56%	0.094
3	15%	+ 1.00%/m	21%	45%	69%	0.130
4	20%	+ 1.00%/m	26%	50%	74%	0.181
5	20%	+ 1.25%/m	28%	58%	88%	0.252
6	25%	+ 1.40%/m	33%	67%	100%	0.350

Rate/month is additional recovery for every month thereafter

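### The protocol says the TITE-CRM will ensure that grade 3–5 risk does not exceed 35%, but the design limits only the predicted risk

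*Protocol article*

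**What the plan says.** The DSMC section of the protocol states, without qualification, that "The TITE-CRM model will ensure that the risk of grade 3–5 toxicity" does not exceed 35%. It goes on, introduced by a contrasting word, to the committee's monitoring of related grade 5 events. It gives one numeric rule: three related grade 5 events among a level's first ten patients close that level and those above it. The same section has the committee review adverse events every six months.

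The operative rule is under Dose assignment procedure. The model is to "assign the highest dose with a predicted risk of grade 3 toxicity of 35% or less". (It names grade 3 only; the endpoint and the weighting rule cover grades 3–5, and it is read that way here.) "Accrual will start at Level 1", and "data from patients who have not completed the 1-year follow-up period are weighted according to the proportion of follow-up completed". Two restrictions apply: "Dose levels may only increase one level between consecutive patients", and no move up "unless there is at least 2 years of cumulative observations on patients at the current dose level".

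The Primary endpoint section says: "The MTD is the recovery factor equation associated with a ≤ 35% rate of grade 3-5 treatment-related toxicity occurring within 1 year of treatment". Table 4 lists the initial risks, headed "Estimated risk of DLT for initial TITE-CRM model", rising from 0.034 at Level −1 to 0.350 at Level 6.

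**The concern.** A rule that keeps an estimate at or below 35% does not keep the true risk there. A rule that takes the highest level meeting that condition also steers towards the limit, so an estimate that is too low leads directly to assignment above it. The restrictions govern how fast the level rises; neither caps the risk of the level in use.

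Two things are at stake. Anyone relying on the DSMC section may take grade 3–5 risk as already controlled, although the committee's only separate numeric trigger cannot respond to grade 3–4 events. And a selected maximally tolerated dose (MTD) may be read as having a true one-year risk of at most 35%, which 48 patients spread over up to eight levels cannot establish.

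**Working it through.** **1. The plan's own figure.** Six patients per level × 8 levels = 48, as stated. The article gives no operating characteristics for the 35% statement, so there is no further figure to reproduce.

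**2. Claim against rule.** The DSMC section speaks of the risk itself. Dose assignment procedure speaks of the predicted risk, with no probability bound on exceeding 35%. The first patients are assigned before any data exist. The contradiction is visible without calculation.

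**3. Estimate versus truth, simplest case.** If a level's true risk is 45%, the observed rate is still at or below 35% with probability P(X ≤ 2 | n = 6) = 0.442, or P(X ≤ 3 | n = 10) = 0.266. The CRM borrows across levels, so this only illustrates the gap.

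**4. Simulation of the stated rules.**
- From the protocol: Table 4 risks s_j, start at Level 1, highest level with predicted risk ≤ 0.35, weight w = follow-up/12 (w = 1 after a grade 3–5 event), both restrictions, n = 48, 12–16 patients a year.
- Assumed, because not stated: p_j(β) = s_j^exp(β), β normal with mean 0 and variance 1.34; full follow-up; lowest level used if none is predicted at or below 35%; the true curves; event times uniform over 12 months, with a late-onset variant where marked †. The grade 5 closing rule was not applied in the † rows.
- A patient contributes p_j after an event and 1 − w·p_j otherwise.

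| True risk, Levels −1 to 6 (%) | Trials selecting a level truly above 35% | Patients of 48 treated above 35% |
|---|---|---|
| 5, 7, 10, 14, 20, 28, 38, 50 | 53% | 9–11 |
| 8, 12, 16, 22, 30, 40, 50, 60 | 44–48% | 12–14 |
| 10, 15, 20, 28, 38, 48, 58, 68 | 56–63% | 19–20 |
| 20, 28, 38, 48 and rising | 54–57% | 24–25 |
| 5, 8, 13, 22, 34, 45, 55, 65 † | 28–39% | 0.26–0.35 × 48 ≈ 12–17 |
| 15, 25, 34, 42, 50, 58, 66, 72 † | 24–35% | 0.34–0.50 × 48 ≈ 16–24 |
| 6, 10, 14, 19, 25, 31, 35, 45 † | 4–5% | 0.01–0.02 × 48 ≈ 0.5–1 |
| Table 4 risks † | 0% | 0 |
| 40, 43, 46, 50, 54, 58, 62, 66 † | 100% | 48 |

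The first four rows use 800 trials each at 12 and 16 patients a year (Monte Carlo standard error about 1.8 points); the † rows use 1,000 trials each at 14 a year. Repeat runs of 400–500 trials gave 44–65% over the first four curves, and 20–33% of trials for curves with a level at 34%. One curve of that kind gave about 7 patients. Hence the overall 20–65% and 7–25 patients. With a prior standard deviation of 0.7, or with posterior-mean risk, three of the curves stayed at 45–57%.

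**5. Size of the excess.** On the first four curves most selections above 35% are of the 38% or 40% level; only 6–14% of trials select a level at 45% or more. Overall event rates over the 48 patients are 22–34%. On the curve with 34% at Level 3 and 45% at Level 4, every selection above the limit is at 45% or more.

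**6. The grade 5 trigger.** P(X ≥ 3 | n = 10, p) = 0.012 at a true grade 5 risk of 5%, 0.070 at 10%, 0.322 at 20%. Ten grade 3–4 events in ten patients would leave the count at zero.

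**The case against.** The strongest reply is that the operative rule is stated correctly as a predicted risk, so the DSMC sentence is loose wording and correcting it changes no assignment, endpoint or sample size. It is true that the assignments do not change. But the sentence is an affirmative safety claim in the safety-monitoring section about the primary endpoint, and no unseen document can make it true.

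Several stronger readings are tempting and are not supported:

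- **That the selected level exceeds 35% about half the time.** This holds for curves where 35% falls between two levels, such as 28% and 38%. With a level at 34% the share is 20–39%; with Level 5 at exactly 35% it is 4–5%; under Table 4 it is 0%. The figure depends on the curve.
- **That the DSMC has no grade 3–5 information.** It reviews adverse events every six months and decides uncertain attribution. Related grade 3–5 events are reportable within one business day, enter the model at full weight and can lower the next assignment, including to Levels 0 and −1. Only a separate numeric grade 3–5 trigger is absent.
- **That the committee's rule covers deaths only because the model is thought to control the rest.** The order of the sentences suggests this; the protocol does not say it.
- **That ethics boards or sites were given a false assurance.** What those bodies received is not shown.

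It is also fair that simulations, posterior summaries and intervals often sit in an analysis plan or committee charter. Their absence from the article is not the fault; they are proposed as support for a corrected sentence.

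**Conclusion.** The sentence is wrong as written: the design targets an estimated risk of at most 35% and does not ensure a true one. That conclusion rests on the text alone.

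The size rests on an assumed power model, prior, event timing and true curves. Where true risk exceeds 35% from Level 5 or lower, the selected level is truly above 35% in roughly 20–65% of trials and about 7–25 of 48 patients are treated above it. The excess is often slight, but not always. If only the top level exceeds 35% the problem nearly disappears, and if Table 4 is right it does not arise. If every level exceeds 35%, all treated patients are above it; a stopping rule in the full protocol could reduce their number but not protect those already treated. The simulations do not show that overall toxicity in the trial would usually be above 35%: on the first four curves it was not.

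**What to change.** Replace the sentence in the DSMC section with: *The TITE-CRM targets the highest level with estimated risk at or below 35%; it does not guarantee that the true risk of an assigned or selected level is at or below 35%.*

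Support it in three ways:

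- State, over a range of true curves, the simulated probability of selecting a level above 35% and the expected number of patients treated above it, using the trial's actual model and prior.
- At each semi-annual review, give the DSMC for each level the grade 3–5 count, the patient-months of follow-up and the model's posterior probability that risk exceeds 35%. Whether any of these carries a numeric action threshold is for the sponsor and the DSMC to decide.
- Report the estimated risk at the selected MTD with a credible interval.

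The cost is one paragraph, a short simulation and a standing table. No extra patients and no change to the assignment rule are needed. The price is a less favourable stated safety property.

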## Discussion

The increasing use of reirradiation in cancer care is likely a result of several underlying factors, including the improved longevity of cancer patients, the availability of better technologies to detect recurrence, the increased conformality of radiation planning, and the development of highly precise radiation delivery techniques [1, 2]. However, high-quality clinical evidence to support reirradiation is sparse, and the optimal reirradiation doses are unknown. When delivering radiation in a previously irradiated area, the treating team must balance two competing priorities: the need to maximize the amount of radiation delivered to tumor (to prevent or delay cancer-related morbidity and mortality) vs. the need to minimize the radiation dose to normal tissues (to avoid causing harm). To balance these trade-offs, a better understanding of the tolerance of thoracic organs to reirradiation is urgently needed. REPAIR will address this need by systematically and carefully increasing the allowable radiation recovery factor, with the goal of allowing the delivery of higher doses to tumor while keeping toxicity rates low.

The TITE-CRM trial design is well-suited to dose-escalation when long-term toxicities are a concern. Standard phase I dose escalation trials use a 3 + 3 design, particularly in the setting of systemic therapy, which delivers the treatment to 3 patients, and then pauses accrual to allow time to observe those patients for toxicities of interested before escalating the dose in the next cohort. While this works well for short-term toxicities, treatments that are associated with long-term toxicities are not well-suited to the 3 + 3 design, since long pauses in accrual would be required. TITE-CRM is a model-based escalation protocol that keeps accrual open without pauses during the trial, uses the information from previously enrolled patients to calculate toxicity probabilities, which allows phase I radiation trials to be completed with a modest sample size in relative short periods of time [36].

There are several important limitations to REPAIR. First, there are uncertainties in dose accumulation, and variability can occur when using different image registration techniques [33]. We will attempt to understand this variability using central collection of plans for analysis, and will mitigate this variability by requiring completion of test plans at each site prior to accrual, and by offering the use of Morfeus image registration technology as part of the trial. Second, REPAIR applies a single recovery factor to all organs, but individual organs may differ in their capacity for radiation repair. This recovery factor is not adjusted for other factors known to predispose to toxicity, such as diabetes and immunosuppression. More advanced models are required, and will likely be developed, to account for individual organ recover while accounting for other risk factors. Finally, although REPAIR can compare outcomes for patients across the different dose levels within the trial, ideally randomized trials of reirradiation will be conducted to best assess the benefits of reirradiation at different levels of recovery.

In summary, the REPAIR trial will use a TITE-CRM dose escalation technique to determine the maximum allowable recovery of normal tissues in the reirradiation setting. The results are expected to assist physicians, physicists and dosimetrists in optimizing the balance between tumor control and risks of toxicity, to ultimately minimize both cancer- and treatment-related morbidity and mortality for patients undergoing reirradiation.

